**Methods::**

The study plan to recruit adult patients (18–75 years, n = 120) with NAFLD, range of alanine aminotransferase is 1.5 to 5 times upper limit of normal (ULN) or liver biopsy is confirmed as NASH. Participants will be randomly allocated into 2 groups: formulated food (n = 80) and a placebo group (n = 40) for 24 weeks. Both groups will receive lifestyle and nutritional advice. The primary endpoint is a decrease in MRS-PDFF by more than 30% from baseline at 24 weeks. The secondary endpoints include the change of anthropometric, liver function, glycolipid metabolism, and systemic inflammation at 4, 12, and 24 weeks. In addition, we consider the changes in intestinal microbiota as an exploration to assess the abundance and diversity at 24 weeks. Weeks 24 to 36 are the follow-up period of drug withdrawal.

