### Dosing rationale

2.5

In the pre-test, patients took 40 g formulated food every day for 12 weeks without any adverse drug reactions, including diarrhea, nausea, constipation, and so on. Therefore, this test selected dose of formulated food 40 g/day to avoid adverse reactions.

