### Sample size estimation

2.10

The sample size was calculated using Medcalc version 18.2.1 software. On the basis of the results of the pre-test, we expected the formulated food to improve the ratio by about 50% and about 13% in the placebo group, with an α level of 2-sided type I error of 0.05, with a β level of type II error of 0.02. The placebo group was calculated to be 35 patients. Because the formulated food group vs the placebo group is 2:1, the total number is about 120 taking into account the 10% shedding rate.

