### Statistical analyses

2.11

This study will use intent-to-treat patient population. Values with a bias distribution will be log transformed before analysis. Baseline characteristics, categorical variables will be tested by χ^2^, and continuous variables will be compared by *t* test. Repeated measures analysis of variance (ANOVA) will be used for variables measured over time to test treatment efficacy, time, and interaction between them. To compare differences between baseline and 24 weeks, paired *t* tests will be used for primary and secondary outcomes (liver function biomarkers, diabetic biomarkers, liver fat content, diabetic biomarkers, lipid biomarkers, BMI, WHR). Secondary analysis will be performed in all participants who completed 24 weeks of intervention and had a drug intake rate of ≥80%, and cases with missing data would be excluded from the analysis. In all analyses, a 2-sided *P* value 0.05 will be considered significant. The frequency of the AE will be assessed using a χ^2^ test.

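### The chi-square test fixed for adverse events has no rule for small counts, and for rare events its false positives at 80 vs 40 fall almost wholly on the side that makes the product look safer

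*Protocol article*

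**What the plan says.** Section 2.11 (Statistical analyses) closes with the only method named for adverse events: "The frequency of the AE will be assessed using a χ^2^ test". Just before it stands the general rule: "In all analyses, a 2-sided *P* value 0.05 will be considered significant". Neither sentence mentions an exact test, a continuity correction or a rule for small expected counts.

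The arm sizes come from the abstract: "formulated food (n = 80) and a placebo group (n = 40) for 24 weeks". Section 2.10 confirms the 2:1 split.

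No adverse event rate is stated. The nearest information is in section 2.5 (Dosing rationale), which reports that in a pre-test "patients took 40 g formulated food every day for 12 weeks without any adverse drug reactions". The size of that pre-test is not given. Section 2.6 has all adverse events recorded, and section 2.8.3 bases safety on adverse events together with laboratory tests, physical examination and vital signs.

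**The concern.** The chi-square P value is a large-sample approximation. In a 40-patient placebo arm it has little to work with when only a few patients have the event. The 2:1 split also makes the approximation lopsided. One or two events that land by chance in the smaller arm form a large relative imbalance, while the same number in the larger arm forms a small one. For rare events, the false positives should therefore collect on the side where placebo looks worse.

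In a safety comparison that is the unwelcome direction. Safety is one of the two stated aims in section 2.1, and a chance imbalance of two events could be reported as a significant safety advantage for the product.

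**Working it through.** **The plan's own figure.** The article gives no calculation for adverse events, so the figure to reproduce is the sample size that sets the arms (section 2.10): 13% vs 50%, two-sided α = 0.05, β = 0.02, ratio 2:1.

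- Pooled proportion = (0.13 + 2 × 0.50)/3 = 0.377.
- n(placebo) = [1.960 × √(0.377 × 0.623 × 1.5) + 2.054 × √(0.13 × 0.87 + 0.50 × 0.50/2)]² / 0.37² = (1.163 + 1.002)² / 0.1369 ≈ 34.2, rounded up to 35.
- Total = 35 + 70 = 105, and 105/0.9 ≈ 117, consistent with the stated total of about 120.

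The 80 and 40 are therefore a sound basis for what follows.

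**When counts are sparse.** With m patients in all having an event, the expected placebo count is m × 40/120 = m/3. It is below 5 whenever m is below 15, that is, below 12.5% of 120 patients.

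**One table: 0/80 on product, 2/40 on placebo.**

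- Expected placebo count: 2/3 = 0.67.
- Uncorrected chi-square = N(ad − bc)² / (n₁ n₂ m (N − m)) = 120 × (0 × 38 − 80 × 2)² / (80 × 40 × 2 × 118) = 3,072,000/755,200 = 4.07, P = 0.044.
- Fisher's exact test: the chance that both events fall on placebo is (40 × 39)/(120 × 119) = 1,560/14,280 = 0.109. Every other split of two events is more probable, so the two-sided P is 0.109.
- With Yates' correction, P = 0.21.
- After 10% dropout (72 vs 36), the uncorrected P is 0.0435 and the exact P 0.109.

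**False positives by direction.** Take the same true rate p in both arms. Sum the binomial(80, p) × binomial(40, p) probabilities over all tables with P < 0.05, split by which arm has the higher observed rate. The nominal rate is 2.5% per side. The rates p are assumptions.

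| True rate, both arms | Chi-square: placebo looks worse | Chi-square: product looks worse | Chi-square: total | Fisher: placebo looks worse |
|---|---|---|---|---|
| 1% | 2.7% | 0.0% | 2.7% | 0.4% |
| 2% | 4.1% | 0.0% | 4.1% | 1.2% |
| 3% | 3.8% | 0.1% | 3.9% | 1.9% |
| 5% | 3.0% | 0.6% | 3.6% | 2.3% |
| 10% | 2.7% | 1.7% | 4.4% | 2.1% |

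At 20% and 30% the chi-square sides are 2.7/2.2% and 2.7/2.4%, close to nominal. The imbalance belongs to rare events.

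**Cost of the exact test.** By the same enumeration with unequal rates (product vs placebo), power to flag harm falls as follows when Fisher replaces chi-square throughout:

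- 15% vs 5%: 34% to 27%.
- 10% vs 5%: 10% to 7%.
- 8% vs 0%: 31% to 19%.

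**The case against.** The strongest objection is to the premise. Section 2.5 speaks of adverse drug reactions, over 12 weeks, in a pre-test of unstated size. Section 2.6 records all adverse events, whatever their cause, over a longer study. An overall rate of 10% to 30% is quite possible, and at those rates chi-square is adequate. The test sentence may also mean one overall comparison, not a test of each rare term. This stands: sparsity is an assumption, and the point is confined to rare events and individual adverse event terms.

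The total two-sided error stays below 5% at the assumed rates of 1% to 5%. That stands too, although the total hides the direction.

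The article does not say that the test is uncorrected, and with Yates' correction the 0 vs 2 signal disappears. A small-count rule may also sit in an analysis plan that is not shown. Against this, the article names the test and the significance level without exception, so the wording as it stands permits the misleading result.

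Three stronger readings are tempting, and the documents do not support them:

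- A reader might infer that the test also hides harm, because 7/80 on product against 0/40 on placebo gives P = 0.054. That reflects the sample size and the 2:1 allocation. Fisher's test gives P = 0.094 for the same table, so changing the test does not help.
- A reader might infer that safety as a whole rests on this one test. Section 2.8.3 also uses laboratory tests, examination and vital signs.
- A reader might infer that the trialists intend to read non-significance as proof of safety. The article does not say so.

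**Conclusion.** The point holds in a limited form and is minor. For rare events, the test as named can declare a significant excess on placebo from two events against none (P = 0.044, exact P = 0.109). At assumed equal rates of 1% to 5%, its false positives run at 2.7% to 4.1% on the side that flatters the product and 0.0% to 0.6% on the other. It rests on three conditions: an uncorrected chi-square, arms near 80 and 40, and events well below 10%. Where an adverse event affects 10% of patients or more, the planned test can stay. The primary endpoint is not affected.

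**What to change.** Replace the sentence on adverse events in section 2.11 with wording to this effect: for each arm, report the number and percentage of patients with at least one event, with the risk difference and a score-based or exact 95% confidence interval, and base the safety conclusion on that interval. Where a P value is shown, use Fisher's exact test if any expected count is below 5, and chi-square otherwise. State that a non-significant result is not evidence of safety.

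This needs a few lines of text and no new data. The price is the loss of power shown above. Limiting the exact test to sparse tables contains that loss for commoner events but not for rare ones, which is why the confidence interval, not the P value, has to carry the conclusion.

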## Discussion

3

The dietary supplements have received a lot of attention in recent years. Although some studies have shown that they can improve metabolism, they have not been formally used in clinical practice. The purpose of the double-blind, randomized, placebo-controlled clinical trial is to investigate the efficacy and safety of formulated food in patients with NAFLD. A follow-up plan was made to sequence the stool samples to explore the relationship between intestinal flora, NAFLD, and formulated food. We acknowledge some of the limitations of this research. Inclusion and exclusion criteria are proposed to maximize the safety of enrolled patients, while also reducing the likelihood of extending the results to patients with more severe conditions or those with a higher degree of comorbidity. If formulated food can achieve the desired effect, it will provide a new treatment idea for NAFLD.
